### Interim analysis

An interim analysis will be performed after hospital discharge (after esophagectomy) of the first 10 patients included in the study. The stopping rules are the occurrence of one of the following:> 40% postoperative complication of gastric perforation requiring re-intervention, during or after laparoscopic ISCON and before esophagectomy.> 40% patients having an aspiration pneumonia after laparoscopic ISCON, resulting in a prolonged hospital stay.> 40% patients not able to undergo the planned esophagectomy within 30 days after laparoscopic ISCON, due to complications specifically attributed to laparoscopic ISCON.

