### Data safety monitoring board & monitoring

This study is classified as a medium risk study. Monitoring will be performed in both centers by an external independent Contract Research Organization according to the Study Monitoring Plan. Based upon advice of the Data Safety Monitoring Board (DSMB) of the UMC Utrecht, a DSMB will not be assigned. Instead of a DSMB, an independent Medical Safety Officer -a Professor in Gastroenterology- was assigned to perform ongoing safety surveillance together with the researchers. After the first 5 patients underwent esophagectomy, all serious adverse events (SAEs) will be evaluated with the Medical Safety Officer. After the first 10 patients underwent both surgeries, an interim analysis will be performed which is described in detail below. All SAEs will be reported by the sponsor to the ethical committee and to the Medical Safety Officer.

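### The >40% stopping limits are read only once all of the first 10 patients are home after esophagectomy, although a fifth event of one kind can settle the result earlier; the likely gain from earlier reading is small but nearly free

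*Protocol article*

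**What the plan says.** The Interim analysis section of the protocol article fixes the time of the look: "An interim analysis will be performed after hospital discharge (after esophagectomy) of the first 10 patients included in the study". It then lists three stopping rules, any one of which suffices. Each is a proportion above a threshold:

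- more than "40% postoperative complication of gastric perforation requiring re-intervention, during or after laparoscopic ISCON and before esophagectomy";
- more than "40% patients having an aspiration pneumonia after laparoscopic ISCON, resulting in a prolonged hospital stay";
- more than "40% patients not able to undergo the planned esophagectomy within 30 days after laparoscopic ISCON, due to complications specifically attributed to laparoscopic ISCON".

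The section on the data safety monitoring board and monitoring describes the same look in slightly different terms: "After the first 10 patients underwent both surgeries, an interim analysis will be performed which is described in detail below". It also describes three safeguards that operate earlier. In place of a DSMB, an independent Medical Safety Officer "was assigned to perform ongoing safety surveillance together with the researchers". On reporting, "All SAEs will be reported by the sponsor to the ethical committee and to the Medical Safety Officer". There is also one scheduled early review: "After the first 5 patients underwent esophagectomy, all serious adverse events (SAEs) will be evaluated with the Medical Safety Officer". The article gives no numerical limit and no stated consequence for any of the three.

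The Esophagectomy section plans an interval of 12–18 days after ISCON, with up to 30 days where that cannot be kept.

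**The concern.** A limit of the form 'more than 40% of 10' is a count, and a count can be settled before all 10 patients have been observed. Once five patients have had the same qualifying event, nothing that happens to the remaining patients can bring the proportion back to 40% or below. As written, the limit is still not read until the tenth patient has had ISCON, waited for esophagectomy, undergone it and gone home. Events under the first limit occur before esophagectomy by definition. Those under the second follow ISCON and would generally be known well before that discharge.

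At stake are those of the first 10 patients who have not yet had ISCON when the fifth event is recorded. Treating them cannot change the outcome of the interim analysis. The point concerns only when the existing limits take effect, not their height or the events they cover.

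**Working it through.** **Inputs.** The threshold (more than 40%), the denominator (first 10 included patients) and the time of the look come from the Interim analysis section. The article gives no rate for any of the three stopping events, so the event rate p is an assumption, shown as a range. The value 25% is borrowed from the Safety ISCON section, which expects gastroparesis in up to 25% of patients. Gastroparesis is not itself a stopping event, so this rate is only illustrative.

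**Step 1: limit as a count.** The article reports no error rate or power for the rule, so there is none to reproduce. 4/10 = 40% does not exceed the limit; 5/10 = 50% does. The limit is five or more.

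**Step 2: certainty.** With five events among the first k patients (k = 5 to 9), the proportion at 10 is at least 5/10 = 50%. Between 10 − 9 = 1 and 10 − 5 = 5 of the first 10 are then still to come.

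**Step 3: how often this happens.** For one event type, with independent patients taken in sequence,

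P(five or more by patient k) = Σ C(k, j) p^j (1 − p)^(k − j), summed over j = 5 to k.

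For p = 0.5 and k = 9: (126 + 84 + 36 + 9 + 1)/512 = 256/512 = 50.0%. For k = 10: (252 + 210 + 120 + 45 + 10 + 1)/1024 = 638/1024 = 62.3%.

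| Assumed p | k=5 | k=6 | k=7 | k=8 | k=9 | k=10 |
|---|---|---|---|---|---|---|
| 10% | <0.1% | <0.1% | <0.1% | <0.1% | <0.1% | 0.2% |
| 25% | 0.1% | 0.5% | 1.3% | 2.7% | 4.9% | 7.8% |
| 40% | 1.0% | 4.1% | 9.6% | 17.4% | 26.7% | 36.7% |
| 50% | 3.1% | 10.9% | 22.7% | 36.3% | 50.0% | 62.3% |

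The k = 9 column is the chance that the fifth event falls before patient 10. The k = 10 column is the chance that the limit is crossed at all.

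**Step 4: patients still to come.** The mean number of the first 10 remaining after the fifth event, counting zero when the limit is not crossed before patient 10, is the sum of the columns k = 5 to 9:

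- p = 25%: 0.001 + 0.005 + 0.013 + 0.027 + 0.049 = 0.095, about 0.1;
- p = 40%: 0.010 + 0.041 + 0.096 + 0.174 + 0.267 = 0.588, about 0.6;
- p = 50%: 0.031 + 0.109 + 0.227 + 0.363 + 0.500 = 1.230, about 1.2.

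**Step 5: effect on the chance of stopping.** Five events by some k below 10 imply five or more at 10, and five or more at 10 imply that the fifth was recorded at or before patient 10. Reading the limit as a running count therefore leaves the k = 10 column unchanged.

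**Step 6: the trigger.** One section triggers the look when the first 10 patients have had both surgeries; the other when the first 10 included have been discharged after esophagectomy. The third limit counts patients who cannot have esophagectomy within 30 days. A patient who never has it satisfies neither trigger, so the harm counted by that limit can itself delay the look or, read literally, prevent it. The two descriptions also need not define the same 10 patients. Steps 2 to 5 use the first 10 included.

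**The case against.** The strongest reply is that the monitoring section largely covers the gap. Perforation requiring re-intervention and aspiration pneumonia prolonging a hospital stay would ordinarily be SAEs, so each would reach the Medical Safety Officer and the ethics committee well before patient 10, and SAEs are also evaluated after five esophagectomies. A reader might infer from the timing of the interim analysis that nobody would act until patient 10, or that patients would in fact go on to be operated on after five perforations. The documents do not support that. What stands is narrower: these safeguards are discretionary as described, and the numerical limits are not linked to them.

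A second reply is that a condensed article may leave suspension procedures to the full protocol or to the Study Monitoring Plan it mentions. That is fair for the details of acting on a safety signal. It does not reach the timing of the limits, which the article states.

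A third is that the rates needed for a sizeable effect lie far above what the article anticipates. Its Safety ISCON section cites a meta-analysis of 1152 patients without major complications attributed to ISCON, and considers perforation unlikely. This also stands. Conditional figures look more striking: among trials that cross the limit, the fifth event precedes patient 10 in 26.7/36.7 = 73% at a 40% rate and 50.0/62.3 = 80% at 50%. A reader might infer a large expected saving from these, but they leave out how rarely the limit is crossed at lower rates.

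Finally, one could read the rules as applying continuously. A percentage needs a denominator, however, and the only one offered is the first 10 patients at the interim analysis. If continuous application is intended, the text should say so.

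**Conclusion.** The point holds as an optional to moderate improvement. The limits take effect only at a late single look, although their outcome can be fixed from patient 5 onwards. The chance of this for one event type is under 0.1% at an assumed rate of 10% or less, 4.9% at 25%, 26.7% at 40% and 50.0% at 50%. The benefit is thus confined to the case where ISCON is far more harmful than anticipated, which is the case a stopping rule is meant for.

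For each limit, the mean numbers of patients still to come are upper bounds on patients spared. Two centres recruit, so later patients may already have had ISCON when the fifth event is known, and events under the third limit may be confirmed only at 30 days. The figures assume independent patients, a constant rate and one event type at a time; the article gives no basis for combining the three. The mismatch between the triggers and the third limit does not depend on any assumed rate.

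**What to change.** In the Interim analysis section, keep the three limits and the events they cover unchanged. Add that each limit counts as met when the fifth qualifying event of that kind among the first 10 patients is recorded, with the same consequence that the protocol already attaches to meeting it at the interim analysis. Keep the 10-patient analysis as the latest time at which the limits are applied.

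Reconcile the two trigger descriptions (both surgeries; discharge after esophagectomy) with each other and with the third limit, so that the text says how patients who do not reach esophagectomy enter the count and when the look takes place.

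What happens clinically once a limit is met is for the sponsor and the Medical Safety Officer to specify.

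The cost is a few sentences and a running count of adjudicated events across two centres. That includes timely judgement of whether a stay was prolonged (second limit) and whether a delay is attributable to ISCON (third limit). No extra patients are needed, and the probability of crossing a limit does not change.

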## Abstract

**Background:**

Anastomotic leakage is the most important surgical complication following esophagectomy. A major cause of leakage is ischemia of the gastric tube that is used for reconstruction of the gastrointestinal tract. Generalized cardiovascular disease, expressed by calcifications of the aorta and celiac axis stenosis on a pre-operative CT scan, is associated with an increased risk of anastomotic leakage. Laparoscopic ischemic conditioning (ISCON) aims to redistribute blood flow and increase perfusion at the anastomotic site by occluding the left gastric, left gastroepiploic and short gastric arteries prior to esophagectomy. This study aims to assess the safety and feasibility of laparoscopic ISCON in selected patients with esophageal cancer and concomitant arterial calcifications.

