### Primary outcome

Complications are defined according to the Esophageal Complications Consensus Group (ECCG) and graded according to the Clavien Dindo Classification [1, 17]. The primary outcome measure is the percentage of complications grade ≥ 2 occurring during or after ISCON and before esophagectomy.

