### Sample size

This is a prospective single arm safety and feasibility trial, classified as a “stage 2a Development” study according to the IDEAL recommendations for surgical innovation [19]. Based upon these recommendations, a total of 20 subjects will be included and no formal sample size calculations are performed (10 patients per centre).

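### The three numeric stopping rules cover only part of the primary safety outcome, so all of the first 10 patients could have a severe ISCON complication without any rule firing

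*Protocol article*

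**What the plan says.** The Primary outcome section of the protocol article defines the safety endpoint without restriction by type of complication: "The primary outcome measure is the percentage of complications grade ≥ 2 occurring during or after ISCON and before esophagectomy".

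The Interim analysis section fixes when the rules are applied: "An interim analysis will be performed after hospital discharge (after esophagectomy) of the first 10 patients included in the study". It then says "The stopping rules are the occurrence of one of the following" and lists three items, each with a limit of more than 40%:

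- Rule 1: more than "40% postoperative complication of gastric perforation requiring re-intervention, during or after laparoscopic ISCON and before esophagectomy".
- Rule 2: more than "40% patients having an aspiration pneumonia after laparoscopic ISCON, resulting in a prolonged hospital stay".
- Rule 3: more than "40% patients not able to undergo the planned esophagectomy within 30 days after laparoscopic ISCON, due to complications specifically attributed to laparoscopic ISCON".

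The section on the data safety monitoring board and monitoring says that no such board is appointed. An independent Medical Safety Officer carries out continuing surveillance with the researchers, serious adverse events are evaluated after the first 5 esophagectomies, and all serious adverse events go to the ethics committee and to the officer. No numeric criterion is given for any of these.

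**The concern.** The final safety statement, and with it the decision to go on to a randomized trial, rests on the primary outcome. The only numeric stopping criteria do not count that outcome. Rules 1 and 2 each count one type of complication with an added condition. Rule 3 is open to any type of complication, but only if it keeps the patient from esophagectomy by day 30.

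Other severe complications of the added operation are therefore outside the rules if the patient is still resected in time. Bleeding that needs re-operation and a cardiac event are examples. They are foreseeable here. The abstract ties the risk factor used for selection to "Generalized cardiovascular disease, expressed by calcifications of the aorta and celiac axis stenosis on a pre-operative CT scan", patients up to ASA III may enter, and the Laparoscopic ISCON section describes clipping the left gastric artery and dividing the short gastric vessels.

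What is at stake is the meaning of the interim look. The trial could pass all three rules while its own primary safety result is already poor, and whether it continues would then depend on judgement alone.

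**Working it through.** **Inputs.** The interim sample is 10 patients, with three separate limits of more than 40% (Interim analysis). The primary outcome is grade 2 or higher between ISCON and esophagectomy (Primary outcome). Gastroparesis is expected in up to 25% (Safety ISCON). The article gives no patient counts for the limits and no chance of stopping, so there is no figure of its own to reproduce.

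**Assumptions.** I count patients with at least one event and use the first 10 included patients as denominator. The monitoring section instead refers to 10 patients who have had both operations. The two wordings need to be reconciled, because rule 3 concerns patients who could not have the second operation in time.

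**Step 1: the limit as a count.** 4/10 = 40% does not exceed 40%; 5/10 = 50% does. Each rule needs at least 5 of 10.

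**Step 2: severe complications outside rules 1 and 2.** Suppose all 10 patients have one and all are resected by day 30. The counts are 0, 0 and 0, and no rule fires. The same holds if up to 4 of the 10 miss day 30. Rule 3 fires from 5 onward, so at least 6 must be resected in time. The observed rate is 10/10, with exact 95% lower limit 0.025^(1/10) = 0.69.

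**Step 3: no pooling.** Take 4 perforations with re-intervention, 4 aspiration pneumonias with prolonged stay and 2 other severe complications, in 4 + 4 + 2 = 10 different patients. Rules 1 and 2 each stand at 4/10. If at most 4 patients miss day 30, nothing fires, although all 10 are affected.

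**Step 4: how much rule 3 protects.** Suppose all 10 have a severe complication outside rules 1 and 2, and each independently prevents timely surgery with assumed probability q. Rule 3 fires with probability P(X ≥ 5) = Σ C(10,j) q^j (1−q)^(10−j), summed over j = 5 to 10:

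| q | 10% | 20% | 30% | 40% | 50% |
|---|---|---|---|---|---|
| rule 3 fires | 0.002 | 0.033 | 0.150 | 0.367 | 0.623 |

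**Step 5: what a direct count would do.** The same formula applies, with p the true proportion of patients with the counted outcome. The rates are assumed and the limits are for scale only:

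| p | 20% | 30% | 40% | 50% |
|---|---|---|---|---|
| at least 5 of 10 | 0.033 | 0.150 | 0.367 | 0.623 |
| at least 4 of 10 | 0.121 | 0.350 | 0.618 | 0.828 |

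**Step 6: a check on counting all grade 2 or higher events.** The article does not give the Clavien-Dindo grade of the expected gastroparesis. If it were graded 2 or higher and occurred at the upper figure of 25%, it alone would reach 5 of 10 with probability 0.078 and 4 of 10 with probability 0.224. A count of every grade 2 event could thus be driven by a complication that the investigators already expect.

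**The case against.** Nothing obliges a stopping rule to equal the primary endpoint, and the two sections do not contradict each other. Event-specific rules plus a feasibility rule are a legitimate design for a descriptive 20-patient development study. The choice of events is reasoned in the Safety ISCON section, which explains the watch for perforation and links gastroparesis to aspiration pneumonia. That section also cites a meta-analysis of 11 retrospective studies with 1152 patients and no major complications attributed to ISCON, so ten severe complications in ten patients are not a likely course.

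Most of this stands as a limit on the size of the point. The ten-of-ten case shows what the rules can miss; it is not a forecast. The prior evidence is retrospective and, as the article says, from unselected patients, so it does not remove the need for a rule that can register unforeseen harm in this cohort.

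Two stronger readings are tempting and not supported:

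- A reader might infer that passing the interim look says nothing about the primary outcome. It says something: rules 1 and 2 capture parts of that outcome, and rule 3 captures any complication attributed to ISCON, death included, that blocks surgery by day 30.
- A reader might infer that severe harm would go unseen. The officer's continuing surveillance, the 5-patient review and the reporting of all serious adverse events could each prompt action before the tenth patient. The full protocol, which is not shown, may say how these reviews are conducted.

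I leave splenic ischemia out of the examples, because the article links it to radiological embolization.

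**Conclusion.** The point holds as one of partial coverage. The numeric rules see perforation with re-intervention, aspiration pneumonia with prolonged stay, and failure to reach surgery by day 30 because of ISCON, each counted separately with a limit of 5 of 10. Other severe complications count toward none of them when surgery still takes place in time. An observed rate of 10/10 is therefore compatible with no rule firing, provided no single rule reaches 5 of 10.

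It would be possible to say that the chance of stopping is 0% at any true rate of unlisted events with timely surgery. That is true only because those events are defined as the ones no rule counts, and it does not measure the trial's risk. The article gives no rates from which that risk could be computed.

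The conclusion rests on reading the list as complete. The text supports this: the monitoring section announces that the interim analysis is described in detail, and the rules follow as a closed list. The gap is in the pre-specified numeric criteria and not in oversight as a whole. It merits an amendment because no data safety monitoring board is appointed and these rules are the only numeric criteria stated.

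**What to change.** Reconcile the Primary outcome and Interim analysis sections. At the existing 10-patient look, add a criterion on the number of patients with the primary outcome between ISCON and esophagectomy. Its severe subset (the higher Clavien-Dindo grades, including death) is preferable, so that expected gastroparesis does not drive the count.

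The sponsor and the Medical Safety Officer should set the limit in advance and state beside it the chance of stopping at several assumed true rates, in the form of the table in step 5. The same count can be tabulated at the 5-patient review of serious adverse events without a separate numeric rule. The figures above cover a single look at 10 patients and would not describe a rule applied twice.

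The cost is one amendment, using data already collected and the officer already in place. The downside is a somewhat higher chance of pausing a trial whose ISCON is acceptable. The chosen limit controls this, and stating the stopping probabilities makes it visible.

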### Postoperative management ISCON

Patients are allowed to drink liquids, soup and supplemental nutrition drinks (high energy, high protein oral nutritional supplements) on postoperative day 0. All patients will have a form of liquid or solid enteral nutrition between ISCON and esophagectomy. Patients will be eligible for discharge on postoperative day 3, depending on the clinical course. A dietician will be consulted to ensure that the patient is optimized in terms of nutrition between ISCON and esophagectomy. All patients will receive a mandatory outpatient clinic standard follow-up appointment on postoperative day 6–8, unless they are still admitted at the hospital. Patients will be re-admitted 0–1 day before esophagectomy.

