### Safety ISCON

A meta-analysis on ISCON was published in 2017 including 11 retrospective studies and a combined total of 1152 patients. None of the included studies reported any major complications associated with the ISCON procedure itself [16]. This indicates that this procedure can be safely performed in unselected patients. Furthermore, since major calcifications of the thoracic aorta according to the UCS score have a relatively high prevalence (30%), we postulated that this meta-analysis likely also include a proportion of patients with major aortic calcification, and that ISCON could thus also be safe in these selected patients [13]. None of the retrospective studies reported perforation due to ischemia after ISCON. Hence, we will remain vigilant for this complication, but deem the chance of it occurring slim. Based upon prior clinical experience in the University Hospital of Cologne, we expect gastroparesis to occur in up to 25% of patients. Since patients with gastroparesis could be at an increased risk of acquiring an aspiration pneumonia, patients’ intake and complaints as nausea and vomiting will be closely monitored and gastroparesis will be treated by emptying the stomach via nasogastric tube placement. None of the retrospective studies report on gastroparesis and nutritional intake after ISCON. This could be explained due to the retrospective data collection. In the current study we use a clear definition of gastroparesis and will prospectively collect nutritional intake data which strengthen the study. Importantly, as mentioned, the meta-analysis included only retrospective studies and had a high degree of heterogeneity with regards to selection of patients, the time interval between ISCON, which arteries are occluded and the technique that is used for ISCON (radiological versus laparoscopic) [22]. The safety and feasibility of ISCON in selected patients have not yet been demonstrated in a prospective trial.

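### Each stopping rule needs at least 5 of the first 10 patients, so a single rule seldom fires at event rates up to about 20%, and four perforations in ten would not stop the trial

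*Protocol article*

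**What the plan says.** The Interim analysis section of the protocol article sets a single look: "An interim analysis will be performed after hospital discharge (after esophagectomy) of the first 10 patients included in the study". It then states: "The stopping rules are the occurrence of one of the following". Three items follow, each with its own limit of more than 40%:

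- Rule 1: more than "40% postoperative complication of gastric perforation requiring re-intervention, during or after laparoscopic ISCON and before esophagectomy".
- Rule 2: more than "40% patients having an aspiration pneumonia after laparoscopic ISCON, resulting in a prolonged hospital stay".
- Rule 3: more than "40% patients not able to undergo the planned esophagectomy within 30 days after laparoscopic ISCON, due to complications specifically attributed to laparoscopic ISCON".

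The Safety ISCON section describes what is expected for perforation: "None of the retrospective studies reported perforation due to ischemia after ISCON", and "Hence, we will remain vigilant for this complication, but deem the chance of it occurring slim". It gives no expected rate for any of the three stopping events.

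The section on the data safety monitoring board and monitoring says that no board is appointed. Instead it provides a Medical Safety Officer with ongoing surveillance, a review of serious adverse events after five patients have had esophagectomy, reporting of all such events to the ethics committee and the officer, and external monitoring. It attaches no numeric trigger to any of these. It also times the interim analysis by the first 10 patients who have had both operations, not the first 10 included.

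**The concern.** In a trial whose stated aim is safety, the stopping rules should have a fair chance of reacting when harm is well above what is expected. Here a limit of more than 40% is applied to each event separately, at one look, with a denominator of 10. Perforation is thought very unlikely, yet rule 1 lets the trial continue after four perforations needing re-intervention. Patients with perforation and patients with pneumonia are not added together, so harm spread over different events can stay below every limit. These are the only safeguards in the article with a number attached, so passing the interim look could be read as stronger evidence of safety than it is.

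Two wording points bear on what is counted. Rule 2 depends on a prolonged hospital stay, while the section on postoperative management after ISCON says "Patients will be eligible for discharge on postoperative day 3, depending on the clinical course". Whether a pneumonia that starts at home and leads to readmission counts is therefore unclear. And if the denominator is patients who had both operations, patients who never reach esophagectomy, whom rule 3 exists to count, could drop out of it.

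**Working it through.** **Inputs from the article.** n = 10, one look, three separate rules, each with a limit of more than 40%. The article states no stopping probability, so there is no figure of its own to reproduce.

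**Assumed inputs.** True event rates (a range is shown) and the overlap between events.

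**Step 1: the count needed.** 4/10 = 40% does not exceed 40%; 5/10 = 50% does. Each rule needs at least 5 of 10.

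**Step 2: one rule.** P(stop) = Σ C(10,k) p^k (1−p)^(10−k) for k = 5 to 10.

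| True rate p | P(at least 5 of 10) | P(at least 4 of 10) |
|---|---|---|
| 10% | 0.16% | 1.3% |
| 20% | 3.3% | 12.1% |
| 30% | 15.0% | 35.0% |
| 40% | 36.7% | 61.8% |
| 50% | 62.3% | 82.8% |

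A 50% chance of stopping needs a true rate of about 45%; an 80% chance needs about 58%. The last column shows that reading the limit as 40% or more would still leave a low chance at 10%.

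**Step 3: rule 1 against the stated expectation.** Four perforations in 10 is an observed 40%, with an exact 95% confidence interval of 12% to 74%. Rule 1 does not fire.

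**Step 4: all three rules, events mutually exclusive, 20% each.** Two rules can fire together only with a 5 + 5 split. So P(any rule) = 3 × 0.03279 − 3 × C(10,5) × 0.2^10 = 0.09838 − 3 × 252 × 0.0000001024 = 0.0983, or 9.8%. In this case 60% of patients have an event, and the same limit applied to patients with any event gives P(at least 5 of 10 at p = 0.6) = 83.4%.

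**Step 5: allowing for rule 3 being partly composite.** Keep 20% perforation, 20% pneumonia and 20% missing surgery through some other ISCON complication. Let a fraction of the perforation and pneumonia patients also miss surgery, so that rule 3's rate rises. Results by simulation:

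| Perforations that block surgery | Pneumonias that block surgery | Rule 3 rate | Any rule fires |
|---|---|---|---|
| none | none | 20% | 10% |
| half | none | 30% | 21% |
| all | none | 40% | 40% |
| half | half | 40% | 40% |
| all | half | 50% | 64% |

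In the limit where every perforation and pneumonia blocks surgery, rule 3 becomes the any-event count and fires 83% of the time. The gap therefore comes from events that do not block surgery.

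**Step 6: a concrete case.** Four perforations, four pneumonias and two other patients unable to have surgery affect all ten patients. No rule fires if at most two of the first eight also miss surgery (2 + 2 = 4). With three, rule 3 reaches 3 + 2 = 5 and fires.

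**The case against.** The strongest reply is that rule 3 already pools a good deal. It covers any ISCON-attributed complication that prevents esophagectomy within 30 days, and a patient who dies of such a complication before resection meets its wording. A reader might infer that death, or a grade 2 or higher complication, counts for nothing; the text does not support that. What stands is that no death stops the trial on its own and that rule 3 also needs five of ten.

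A reader might also infer that passing the interim look is nearly certain even when the procedure is clearly harmful. That goes too far: a single rule fires 15% of the time at a 30% rate and 37% at 40%, and the 9.8% in step 4 is the low end of a range that depends on overlap.

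Nor are these rules the only protection. The Medical Safety Officer, the review after five patients and the reporting of serious adverse events could prompt action sooner. They have no stated trigger, so they do not change how the rules perform.

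It is tempting to turn the 1152 patients of the cited meta-analysis into an upper bound for the perforation rate. The article says only that no perforation was reported, in retrospective studies of unselected patients, and that is not zero observed among 1152 patients like those enrolled here.

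Rule 2 also lacks the end point at esophagectomy that rule 1 has. This makes rule 2 broader, not weaker, so it is a matter of clarity only.

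Finally, a condensed article need not print a rationale or operating characteristics. The point does not rest on their absence: the event, limit, denominator and way of combining are all stated.

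**Conclusion.** The concern holds as a weakness of rules that the article states in full. Each rule needs 5 of 10, and a given rule fires 0.2%, 3.3% and 15% of the time at true rates of 10%, 20% and 30%. The clearest mismatch is perforation: a chance described as slim sits beside a rule that tolerates four in ten. Across the three rules, at 20% each, the chance of stopping is about 10% with exclusive events and roughly 20% to 64% under the assumed overlaps, against 83% for a count of patients with any event. All event rates and overlap fractions are assumptions, because the article gives none. The description of a rule that seldom fires applies to single-event rates up to about 20%, not to every level of harm. Severity: should be fixed.

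**What to change.** 1. Apply the existing limit of more than 40% to the number of patients with any of the three events or death before esophagectomy.
2. Item 1 alone would still let four deaths in ten pass. The sponsor and the Medical Safety Officer should therefore reconcile the perforation limit, and decide on any separate limit for death, in line with the Safety ISCON section, using binomial operating characteristics such as those above. No value is proposed here.
3. State the time window of rule 2 and whether an aspiration pneumonia that causes readmission counts.
4. Reconcile the two descriptions of the interim denominator (both operations done, or the first 10 included), so that patients who never reach esophagectomy are counted under rule 3 and do not leave the look without a defined time.

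The cost is one amended paragraph and a small table. The downside is a somewhat higher chance of an unnecessary pause: the any-event count fires 3% of the time if 20% of patients have an event, and 15% if 30% do.
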